***Statistical tests:***

Mean difference between independent groups will be analyzed by Student’s t test or Mann-Whitney U test.

Mean difference between paired groups will be analyzed by paired t test or Wilcoxon’s signed rank test.

For the primary outcomes, changes from baseline will be analyzed by generalized linear model controlling for age, sex, weight, and smoking (yes or no) and drinking (yes or no) habits. Every interaction will be tested and included if it decreases Akaike’s information criteria.

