# STUDY DESIGN

This is a single-center, randomized, double-blind, placebo-controlled, 2-arm parallel group study. This study will consist of a 30 days administration period.

The planned sample size for this study is 50 healthy older adults, with 25 subjects randomized equally to each of the two-study arms in a double-blind manner.

| **Study Arm** | **Subject Number** |
| --- | --- |
| Krill Oil | N = 25 |
| Placebo | N = 25 |
| **Total** | **N = 50** |

In order to evaluate the goals of the study, assessments will be conducted at Visit 1 (Day 1) before administration of the test supplement (baseline), and Visit 3 (Day 31). Subject will visit or will be contacted by phone after 2 weeks of ingestion (Visit 2) in order to monitor adverse events and changes in concomitant medications as well as to foster compliance with the study dosing regimen.

The study will be conducted at a single site at Fukushima Orthopedic Clinic, Tochigi, Japan.

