**Removal by Qualified Investigator:**

Subject may be discontinued at the discretion of the Qualified Investigator. A subject leaving the study prematurely will not be replaced by another. Criteria for removal of subjects from the study will include:

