# STATISTICAL EVALUATION

## Determination of sample size

Sample size is set according to the report by Maki et al. [6], in which the administration of krill oil (2 g/d for 4 weeks) showed significant differences in the plasma EPA & DHA concentrations of 25 participants in the control and krill oil groups.

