**8.2 Analytical Populations**

- The **Safety Population** will consist of all subjects who received any amount of either product, and on whom any post-randomization safety information is available.
- The **Per Protocol (PP) Population** “Per Protocol (PP) Population” consists of all subjects who consumed at least 80% of test or placebo doses do not have any major protocol violations and complete all study visits. Subject who has a compliance of <80% will be deleted from the further analysis.
  1. **Analysis Plan**

An effectiveness analysis based on the per protocol population will be performed. Continuous variables will be tested for normality and log-normality. Log-normally distributed variables will be analyzed in the logarithmic domain. Non-normal variables will be analyzed by appropriate non-parametric tests.

Missing values will be deleted in a pair-wise manner for the comparison, except in the structured questionnaires of JKOM (Q1 – 25) and JOA in which missing data will be deleted in a list-wise manner.

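### Student's equal-variance t test is the only parametric two-group test named for the laboratory outcomes; it would be modestly miscalibrated for EPA and DHA if the analysed arms differ in both size and spread

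*Protocol*

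**What the plan says.** The Statistical tests paragraph fixes the two-group method: "Mean difference between independent groups will be analyzed by Student’s t test or Mann-Whitney U test". It names no unequal-variance version. The two primary outcomes have their own method, a covariate-adjusted generalized linear model of change from baseline. The sentence on independent groups therefore governs the secondary blood and urine outcomes, which include plasma EPA and DHA.

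The Analysis Plan chooses the scale and type of test from the shape of each distribution: "Log-normally distributed variables will be analyzed in the logarithmic domain" and "Non-normal variables will be analyzed by appropriate non-parametric tests". It does not mention checking or allowing for unequal variances.

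Three provisions determine the analysed arm sizes:
- Study Design plans equal arms, "with 25 subjects randomized equally to each of the two-study arms".
- The withdrawal rules state that "A subject leaving the study prematurely will not be replaced by another".
- Section 8.2 adds "Subject who has a compliance of <80% will be deleted from the further analysis", and "An effectiveness analysis based on the per protocol population will be performed".

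The sample size section relies on an earlier krill oil study that "showed significant differences in the plasma EPA & DHA concentrations". It gives no SD, effect size, significance level or power.

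**The concern.** The pooled standard error is right when the variances are equal, and nearly right when the arms are the same size. It goes wrong when both differ. If the smaller arm has the larger variance, the standard error is too small and the test rejects too often. If the larger arm has the larger variance, the test is too cautious.

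The plan guarantees neither equal sizes nor equal spread. Losses are not made up and compliance deletions follow randomisation. For EPA and DHA, subjects on krill oil may differ in how much their levels rise, which would add variance in that arm only. At stake is the calibration of the p-values, and of any intervals reported, for the two exposure markers on which the sample size was based. The direction of the error would depend on which arm happened to lose more subjects.

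There is also a point of wording. The sentence presents the Mann-Whitney test as a comparison of means. When spreads differ it is not one; it addresses whether values in one arm tend to exceed those in the other.

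**Working it through.** **Inputs from the protocol.** Planned arms of 25 and 25; Student's t test; no replacement; deletion below 80% compliance. The figure of 25 per arm is taken by precedent and cannot be re-derived, because no effect size, SD, alpha or power is stated. For orientation only, 25 per arm gives 80% power at two-sided 5% for a standardised difference of about 0.80.

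**Assumptions, none of them in the protocol.** Normal data, two-sided alpha of 5%, ratio r of krill SD to placebo SD of 1.5, 2 or 3, and analysed sizes as listed below.

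**How easily sizes drift apart.** Suppose each subject is lost independently with the same probability in both arms, 10% or 20%. From 25 per arm, the exact binomial chance of equal analysed arms is 19% or 14%. A gap of 3 or more has probability 23% or 37%, and a gap of 5 or more 3% or 11%. Some imbalance is therefore likely under these loss rates even without differential dropout, but large gaps are uncommon.

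**Standard errors.** Take the placebo SD as 1.
- Student: s² = [(n_K − 1)r² + (n_P − 1)] / (n_K + n_P − 2), and SE = √[s²(1/n_K + 1/n_P)].
- Welch: SE = √(r²/n_K + 1/n_P), with Satterthwaite degrees of freedom.

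At 20 krill, 25 placebo, r = 2:
- s² = (19 × 4 + 24)/43 = 2.326, so Student's SE = √(2.326 × 0.09) = 0.457 on 43 df (t = 2.017).
- Welch's SE = √(4/20 + 1/25) = 0.490 on 26.5 df (t = 2.054).
- Half-width ratio = (2.017 × 0.457)/(2.054 × 0.490) ≈ 0.917, so Student's interval is about 8% too narrow.

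At r = 1.5 the same sizes give 0.947, about 5% too narrow. At 25 krill, 20 placebo the ratios are 1.044 and 1.065, so intervals are about 4–7% too wide. At 25/25 the two standard errors are identical and only the degrees of freedom differ; the ratio is 0.983 at its lowest (r = 3).

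**Error rate of Student's test at nominal 5%**, from 200,000 simulated null data sets per cell. The Monte Carlo standard error near 5% is √(0.05 × 0.95/200,000) ≈ 0.05 percentage points.

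| Krill / placebo | r = 1.5 | r = 2 | r = 3 |
|---|---|---|---|
| 25 / 25 | 5.0% | 5.2% | 5.4% |
| 22 / 25 | 5.7% | 6.2% | 6.7% |
| 20 / 25 | 6.1% | 6.9% | 7.7% |
| 25 / 22 | 4.6% | 4.4% | 4.3% |
| 25 / 20 | 4.1% | 3.8% | 3.6% |
| 20 / 20 | 5.2% | 5.2% | 5.4% |

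Welch's test stays between 4.9% and 5.1% in every cell. With equal SDs, Student's test is at about 5% for all these sizes.

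**Cost of Welch's test when variances are equal.** At a standardised difference of 0.8, simulated power for Student's and Welch's tests is 79.1% and 79.0% at 25/25, and 74.2% and 74.0% at 20/25.

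**The case against.** The strongest reply is that nothing is wrong under the design as written: at 25/25 the error does not exceed 5.4% even at r = 3, and equal losses leave it there. That stands. A reader might infer that the compliance rule will unbalance the arms, or that krill oil will raise the EPA and DHA variance. The protocol supports neither as fact, since it forecasts no losses by arm and gives no SD. More extreme cases can be built, such as 18 krill against 25 placebo (7.8% at r = 2), but they need 7 of 25 (28%) lost from one arm and none from the other.

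The spread argument also reaches only EPA and DHA. Nothing in the protocol suggests unequal variances for blood counts, liver enzymes, CRP, MMP-3 or hyaluronic acid. For EPA and DHA an effect is expected, so the equal-means null is unlikely and interval width matters more than false positives. The statistical section promises no confidence intervals, which weakens the point further.

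The log-scale rule may shrink spread that grows with the mean, and removing poor compliers narrows one source of variation. Both are partial: logging applies only to variables judged log-normal, and the compliance rule leaves differences in individual response.

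One could say the choice belongs in the statistical analysis plan. That would be a good answer had the protocol been silent, but it names the pooled-variance test.

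**Conclusion.** A minor, conditional weakness in the choice of test, and not a demonstrated error. The only parametric two-group test named for the laboratory outcomes is sensitive to a combination that the plan permits and does not guard against. With moderate losses from one arm (3 to 5 subjects) and an assumed SD ratio of 1.5 to 2, the true error lies between about 3.8% and 6.9%, depending on which arm is smaller. Whether this happens rests on two assumptions that the protocol can neither confirm nor exclude: unequal analysed arms and a wider krill-arm spread in EPA and DHA.

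It would be wrong to conclude that the efficacy result is affected. The stated model for the primary outcomes is the generalized linear model; no unequal spread is argued for those outcomes, and this point gives no reason to change that model or its standard errors. The Mann-Whitney remark concerns wording only.

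**What to change.** In the Statistical tests paragraph, replace Student's t test by Welch's unequal-variance t test for comparisons between independent groups, applied on the log scale wherever the Analysis Plan calls for it. Report Welch's interval if intervals are given. Describe the Mann-Whitney test as assessing whether values in one arm tend to be larger, and do not label it a test of mean difference. Leave the paired tests and the primary-outcome model as they are.

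The cost is a change of wording. Power falls by about 0.2 percentage points at most in the equal-variance settings checked, and no extra data or subjects are needed. Making the change before the key is opened also avoids choosing between the two tests after the variances have been seen.

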# INTRODUCTION

Krill oil is an edible oil extracted from krill, a small red-colored crustacean found in the Antarctic Ocean [1]. Krill oil is rich in long-chain n-3 polyunsaturated fatty acids in the form of phospholipids [1].

Krill oil reduced tumor necrosis factor-α levels of lipopolysaccharide - stimulated peritoneal macrophages in obese Zucker rats [2]. The anti-inflammatory effect of krill oil was also observed in a rat model of dextran sulfate-induced experimental ulcerative colitis [3]. Krill oil consumption was shown to inhibit the progression of arthritis in an experimental mouse model of arthritis, in which the increase of inflammatory cytokines, IL-1 and IL-13, was suppressed [4]. Also, Deutsch et al. reported that krill oil administration mitigated the subjective symptoms of osteoarthritis as assessed by Western Ontario and McMaster Universities Osteoarthritis Index (WOMAC) and reduced C-reactive protein (CRP) levels in patients with cardiac disease, rheumatoid arthritis, or osteoarthritis with CRP levels greater than 1.0 mg/dL [5]. However, the effect of krill oil on mild knee pain has not yet been determined

The primary objective of this trial is to compare the efficacy of krill oil with a placebo in reducing the subjective symptoms of adults with mild knee pain.

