# STUDY OBJECTIVES

To examine the effect of a 30 days (approximately 4 weeks) of krill oil administration on knee joint pain.

Primary outcomes**:**

- Japanese Knee Osteoarthritis Measure (JCOM)
- The Japanese Orthopedic Association knee rating score (JOA score)

Secondary outcomes**:**

- Blood and urine analysis
- Range of motion (ROM) of the knee

* ROM was deleted from the secondary outcome because of the difficulty to obtain the reliable data.

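### For the secondary blood and urine outcomes the only stated tests are within-arm paired tests and an unadjusted between-arm test; a baseline-adjusted comparison of the arms would serve better

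*Protocol*

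**What the plan says.** The Introduction of the protocol gives the primary objective as a comparison between arms: "compare the efficacy of krill oil with a placebo in reducing the subjective symptoms of adults with mild knee pain". Study Objectives restates the aim without a comparator: "To examine the effect of a 30 days (approximately 4 weeks) of krill oil administration on knee joint pain". It names JKOM (also spelled JCOM there) and the JOA score as primary outcomes, and blood and urine analysis as the secondary outcome; range of motion is struck out.

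The Analysis Plan in the Statistical Evaluation section opens with an effectiveness analysis in the per-protocol population. Statistical tests, which follows, has three parts:

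- A generic between-group line: "Mean difference between independent groups will be analyzed by Student’s t test or Mann-Whitney U test".
- A generic paired line: "Mean difference between paired groups will be analyzed by paired t test", with the Wilcoxon signed-rank test as the alternative.
- A specific method for the primary outcomes: "For the primary outcomes, changes from baseline will be analyzed by generalized linear model controlling for age, sex, weight, and smoking", plus drinking habit.

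The two generic lines name no outcome, arm or role. The between-group line does not say whether it applies to Visit 3 values or to changes. No third method is given for the secondary outcomes.

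**The concern.** Study Design places assessments at Visit 1 (Day 1) and Visit 3 (Day 31) only, and the arms are parallel. A paired test can therefore only set Visit 3 against Visit 1 within an arm. It picks up anything that moves both arms, such as placebo response, regression to the mean, natural course or changes in diet over the month. It does not address the question that the randomisation was set up to answer.

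The generic between-group test does address that question, but without adjustment for the Visit 1 value. The secondary outcomes are measured at both visits, so the plan collects a baseline for each of them and then does not use it to best effect.

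Two things are at stake. One is precision and protection against chance baseline imbalance in the secondary comparisons. The other is that a significant change in the krill arm beside a non-significant one in the placebo arm could be taken for a treatment effect.

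**Working it through.** **The plan's own figure.** The only relevant figure is 25 per arm, 50 in total (Study Design). It cannot be re-derived: the sample size section rests on a cited study of plasma EPA and DHA and gives no effect size, SD, significance level or power. It is not contested here. EPA and DHA are themselves among the secondary laboratory outcomes.

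**1. How many outcomes depend on the generic tests.** Laboratory Analysis lists 8 blood-count, 12 serum, 4 plasma fatty-acid and 2 urine parameters: 8 + 12 + 4 + 2 = 26. Taken literally, the paired line allows 26 × 2 = 52 within-arm tests.

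**2. What within-arm testing would do if read as a comparison.**

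Inputs:

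- n = 25 per arm, from Study Design.
- Two-sided 0.05, assumed.
- True difference between arms zero, assumed.
- Both arms improve by d SDs of change, assumed over a range because the protocol gives no expected placebo change or SD.

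Formulas: p = P(T > t[0.975; 24]), where T is noncentral t with 24 degrees of freedom and noncentrality d√25. The arms are independent, so P(krill significant, placebo not) = p(1 − p).

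| d | p (krill arm significant) | p(1 − p) |
|---|---|---|
| 0 | 0.025 | 0.025 × 0.975 = 0.024 |
| 0.2 | 0.159 | 0.159 × 0.841 = 0.134 |
| 0.3 | 0.302 | 0.302 × 0.698 = 0.211 |
| 0.4 | 0.484 | 0.484 × 0.516 = 0.250 |
| 0.5 | 0.670 | 0.670 × 0.330 = 0.221 |
| 0.8 | 0.970 | 0.970 × 0.030 = 0.029 |

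The product cannot exceed 0.25, so d of 0.3 to 0.5 is the worst region. If the per-protocol population fell to 20 per arm, the values at d = 0.2, 0.3, 0.4, 0.5 and 0.8 would be 0.116, 0.186, 0.239, 0.246 and 0.070.

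**3. The between-arm test under the same conditions.** In 100,000 simulated trials per setting, the two-sample t test on change was significant in 4.9%, 4.9%, 4.9% and 5.0% of trials at d = 0, 0.3, 0.5 and 0.8. Half of the nominal 5%, that is 2.5%, favours krill. The shared improvement cancels.

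**4. Why adjusting for Visit 1 is the better between-arm method.** Let the variance at each visit be σ² and the correlation between visits ρ. In large samples the variance of the estimated difference between arms is (2σ²/n) times:

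- 1, if Visit 3 values are compared unadjusted;
- 2(1 − ρ), if changes are compared;
- 1 − ρ², if Visit 3 is compared adjusted for Visit 1 (ANCOVA).

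Since 1 − (1 − ρ²) = ρ² ≥ 0 and 2(1 − ρ) − (1 − ρ²) = (1 − ρ)² ≥ 0, adjustment is never less precise than either alternative, apart from the cost of one error degree of freedom (25 + 25 − 2 = 48 becomes 47). The protocol gives no ρ, so the gain cannot be put as a number.

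**The case against.** A reader might infer that the paired tests are designated as efficacy tests, because they stand under the effectiveness analysis and one statement of the objective names no comparator. The text does not support that. The paired line is a generic statement of which test suits which data structure, and no sentence says that a within-arm change will be taken as evidence of efficacy. The primary objective is a comparison with placebo. The primary outcomes have a model of their own; its treatment term is implied rather than written, but no other reading serves that objective.

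Nor do the secondary outcomes lack a between-arm comparison: the independent-groups test is available for them. The trial is a pilot, and a statistical analysis plan that is not at hand may fix the role of the paired tests. Asking only for a label on them would be asking for detail that such a plan commonly supplies.

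All of this stands, and it limits the point. It does not touch what the protocol does fix: for the secondary outcomes it prescribes an unadjusted comparison and a test that makes no comparison, although a better method is available from data already collected.

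**Conclusion.** The point holds as a low-cost improvement, mainly for the secondary blood and urine outcomes. It is not an error in the primary analysis.

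The figures of 21% to 25% should not be read as this trial's false-positive rate. They apply only if someone draws a conclusion that the protocol never announces, and only for a shared improvement of 0.3 to 0.5 SD of change. At 0.2 SD the figure is 13%, and at 0 or 0.8 SD it is 2% or 3%, close to the 2.5% of the between-arm test. They also assume normally distributed changes, equal improvement in both arms, 25 analysed per arm and a two-sided 0.05 level. The advantage of baseline adjustment does not depend on those values of d, but its size depends on a correlation that the protocol does not give.

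**What to change.** In Statistical tests:

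- For the secondary blood and urine outcomes, replace the generic tests with a between-arm comparison of the Visit 3 value adjusted for the Visit 1 value (ANCOVA). Use the log scale for variables the plan already sends there, and ranks where it already calls for a non-parametric method.
- Report within-arm change as a descriptive mean or median with a 95% confidence interval.
- State that efficacy statements rest on the between-arm comparison.

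The cost is a few sentences of wording, slightly more analysis work and one error degree of freedom per model. No new data, visits or participants are needed, because both values are already collected.

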## Visit 1 – Screening and enrollment

At screening, a Subject Information and Consent Form will be given to the potential subject. The subject will read the information carefully and will be given the opportunity to seek more information if needed. The subject will also be provided with the option of taking the consent form home to review prior to making his or her decision. If agreeable, the subject will sign the consent form and receive a duplicate. Once consent has been obtained, the following assessment will proceed.

- Review of the inclusion/exclusion criteria
- Review of medical history and concomitant therapies
- Collection of demographic information such as gender, age, alcohol consumption and smoking habits

Eligible subjects will be randomized and take baseline assessment.

Baseline assessments will include:

- Height, weight and BMI
- Japanese Knee Osteoarthritis Measure (JCOM)
- The Japanese Orthopedic Association knee rating score (JOA score)
- Blood and Urine analysis
- Range of motion (ROM) of the knee

Subjects will receive test supplements and administration diary.

Subjects will be instructed in detail by site personnel about the dosing regimen. The first dose of study product is to be taken the day at the dinner on the day taking the baseline assessment (Day 1).

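### The primary models for change in JKOM and JOA leave out the baseline score, which loses precision and leaves an error proportional to any chance baseline imbalance

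*Protocol*

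**What the plan says.** Study Objectives names two primary outcomes, JKOM (also spelled JCOM in the protocol) and the JOA score. Study Design places the measurements so that a pre-treatment value exists: "assessments will be conducted at Visit 1 (Day 1) before administration of the test supplement (baseline), and Visit 3 (Day 31". Both scores are listed among the baseline assessments at Visit 1.

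The Analysis Plan, under Statistical tests, fixes the primary model: "changes from baseline will be analyzed by generalized linear model controlling for age, sex, weight, and smoking", with the list closing on "and drinking (yes or no) habits". One rule allows further terms: "Every interaction will be tested and included if it decreases Akaike’s information criteria". That rule admits interactions only, so it gives no route for a baseline-score main effect. The general between-group comparison carries no covariates at all: "Mean difference between independent groups will be analyzed by Student’s t test or Mann-Whitney U test". No other section of the protocol names baseline JKOM or JOA as a covariate.

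The planned size is 25 per arm. Labeling and Coding describes allocation by a card in an envelope and mentions no stratification.

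**The concern.** The model adjusts for five demographic and habit variables but not for the pre-treatment value of the outcome, which is usually a strong predictor of change. The protocol itself writes the list, so the choice has been made here and not left to a separate analysis plan.

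Two things are at stake. The first is precision: unless r is close to 1, the change score carries baseline noise that a fitted slope would remove. The second is the estimate in the one trial that is run. With 25 per arm, and nothing described that would balance severity at entry, the arms can start apart by chance. Regression to the mean then tends to make the arm that starts worse appear to improve more, whatever it was given.

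**Working it through.** **Nothing to reproduce.** The protocol states 50 subjects, 25 per arm, by reference to an earlier study of plasma EPA and DHA. It gives no effect size, SD, alpha or power for JKOM or JOA, so there is no planned precision to recompute.

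**Inputs.** n = 25 per arm (Study Design). The correlation r between the Visit 1 and Visit 3 scores is not in the documents; it is assumed, and 0.3 to 0.9 is shown. Equal SD s at both visits is also assumed. Detectable differences further assume a two-sided 5% test and 80% power.

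**Step 1, variance per subject.**
- Change score: 2s²(1-r)
- Baseline-adjusted: s²(1-r²)
- Ratio, adjusted to change score: (1+r)/2

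Estimating the slope with N = 50 multiplies the ratio by 1 + 1/(50-4) = 1 + 1/46 = 1.022. At r = 0.5 this gives 0.75 × 1.022 = 0.77.

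**Step 2, detectable difference.** (1.960 + 0.842) × √(2/25) = 0.792 SD of the analysed variable. Multiply by √(2(1-r)) for the change score, and by √((1-r²) × 1.022) for the adjusted analysis. Results are in SDs of the raw score.

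| r | Variance ratio | Detectable difference, change score | Detectable difference, adjusted | Power of adjusted analysis where change score has 80% |
|---|---|---|---|---|
| 0.3 | 0.66 | 0.94 | 0.76 | 93% |
| 0.5 | 0.77 | 0.79 | 0.69 | 89% |
| 0.7 | 0.87 | 0.61 | 0.57 | 85% |
| 0.9 | 0.97 | 0.354 | 0.349 | 81% |

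For r from 0.3 to 0.7, the adjusted analysis matches the precision of 25 per arm on the change score with 17 to 22 per arm (25 × 0.664 = 16.6 and 25 × 0.868 = 21.7, rounded up). That is 3 to 8 subjects per arm. At r = 0.9 the saving rounds to none.

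**Step 3, error given an imbalance.** The standard error of the baseline mean difference is √(2/25) = 0.28 SD. A difference above 0.3 SD in either direction arises by chance in about 29% of such trials. The change-score contrast is off by -(1-r) times the imbalance. For an imbalance of one standard error the size is:
- r = 0.3: 0.7 × 0.283 = 0.20 SD
- r = 0.5: 0.5 × 0.283 = 0.14 SD
- r = 0.7: 0.3 × 0.283 = 0.08 SD

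**Step 4, simulation check.** With 10,000 simulated trials of 25 per arm at each of r = 0.3, 0.5 and 0.7, the variance ratios were 0.66, 0.78 and 0.86. The slope of the change-score estimate on the imbalance was -0.71, -0.49 and -0.31. After baseline adjustment it was about 0.

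**The case against.** The strongest reply is that a change-score model is a legitimate choice. Under randomization its contrast is unbiased on average and its test keeps its nominal type I error, and the trial is labelled a pilot. That stands, and it limits the point to efficiency and to error conditional on the imbalance that occurs.

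Three objections to the size also stand:
- r is assumed. The documents do not rule out a value above 0.7 over a 30-day retest, and near 0.9 the gain is about 3%.
- The formulas compare an unadjusted change score with a model containing baseline only. The planned model already holds five covariates, and these may absorb part of the baseline effect.
- The figures use 25 per arm. Efficacy is analysed per protocol and withdrawals are not replaced, so the analysed number may be lower.

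A reader might infer that baseline imbalance is left uncorrected. It is not: change from baseline subtracts the baseline score in full, which is too much whenever r is below 1 with equal variances. A reader might also carry the criticism over to the laboratory outcomes. The sentence at issue covers only the primary outcomes, and no comparable defect is shown for the laboratory analyses.

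None of this removes the omission. No passage adds the baseline score, and the interaction rule cannot bring it in as a main effect.

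**Conclusion.** The point holds as one of lost precision and conditional error. The primary models omit a pre-treatment covariate that is already collected and directly relevant. Against an unadjusted change score, with equal variances and 25 per arm, the variance saved is about 34%, 23%, 13% and 3% at r = 0.3, 0.5, 0.7 and 0.9. The saving against the planned covariate model may be somewhat less. The loss is material at r of about 0.7 or below and negligible near 0.9.

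It would be wrong to read this as saying that the planned analysis is biased or that its test is invalid. That reading fails for the randomized comparison. The per-protocol set drops subjects after randomization, so balance there is not guaranteed, but that is a separate matter and the figures above do not depend on it. The omission itself is certain from the text. Its size is not, because it turns on an r that the documents do not give. The change is worth making because it costs so little.

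**What to change.** In the Analysis Plan, under Statistical tests, add the baseline value of the same score as a prespecified covariate: baseline JKOM in the JKOM model and baseline JOA in the JOA model. Report the adjusted mean difference between arms with its 95% CI. The outcome can remain change from baseline, since in a linear model containing baseline the treatment estimate is the same for change as for the follow-up score. Make the change before unblinding.

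The cost is a few words and one degree of freedom per model. No new data are needed, and no subject is lost, because everyone with a change score has a baseline score. The one-degree-of-freedom figure is for the main effect only. As the interaction rule is worded, the new term would also become eligible for interactions, so the revised sentence should say whether it does.

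### The primary model keeps any interaction that lowers AIC, so the outcome data choose the model and the treatment test exceeds its nominal error rate

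*Protocol*

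**What the plan says.** The Analysis Plan, under Statistical tests, states that for the primary outcomes "changes from baseline will be analyzed by generalized linear model". The model adjusts for five covariates: age, sex, body weight, and two yes/no indicators, one for smoking and one for alcohol. The sentence after that sets the selection rule, with AIC as the yardstick: "Every interaction will be tested and included if it decreases" that criterion.

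The rule does not limit the candidates to two-way terms or to covariate-by-covariate terms. It gives no order of entry, does not name the treatment contrast to be tested once interactions are in the model, and makes no allowance for the search.

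The data available to support the search are small. Study Design plans 50 participants, 25 per arm. Section 8.2 makes the per-protocol set the basis for efficacy ("An effectiveness analysis based on the per protocol population will be performed"), so the number analysed can be below 50. There are two primary outcomes, JKOM and the JOA score, and the search would be run separately for each.

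**The concern.** The rule lets the outcome data decide which model yields the primary result. This causes two problems.

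First, the test in the selected model is carried out as if that model had been fixed beforehand. Keeping terms because they improve the fit shrinks the residual variance by chance, and where treatment terms are among those kept, it also favours chance treatment patterns. The nominal error rate is then not the real one.

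Second, once a treatment-by-covariate term is in the model, the treatment coefficient is no longer the overall krill-minus-placebo difference. It is the difference at covariate value zero: age 0 or weight 0 if covariates are uncentred, or the reference category for sex, smoking or drinking. What the coefficient means then depends on which terms entered and how the covariates were coded.

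The Introduction gives comparison of efficacy with placebo as the primary objective, and this model is the one assigned to the primary outcomes. The estimate and p-value that answer the trial's main question are therefore the ones affected.

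**Working it through.** **Inputs from the protocol.** Treatment plus five covariates gives six variables. N is at most 50. The protocol gives no alpha, error rate or power to reproduce, so two-sided 0.05 is assumed. N = 40 is an assumed lower case for the per-protocol set.

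**Number of candidates.**
- Two-way: C(6,2) = 15, of which 5 involve treatment.
- All orders: 2^6 − 1 − 6 = 57. A model with the intercept, six main effects and all 57 interactions has 64 parameters, more than the 50 participants.

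**How loose the filter is.** A one-parameter term lowers AIC when its likelihood-ratio chi-square exceeds 2.
- Asymptotically: P(chi-square, 1 df > 2) = 0.157. Expected spurious two-way terms: 15 × 0.157 = 2.4. Chance of at least one, if independent: 1 − (1 − 0.157)^15 = 0.92.
- Finite-sample form for a normal linear model, one interaction added to the main-effects model (8 parameters): the term enters when F > (e^(2/N) − 1)(N − 8). At N = 50 this is 0.0408 × 42 = 1.71, and P(F(1,42) > 1.71) = 0.198. Expected spurious terms: 15 × 0.198 = 2.96. Chance of at least one treatment interaction, if independent: 1 − (1 − 0.198)^5 = 0.67.

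**Null simulation.** The outcome is normal with no treatment, covariate or interaction effect. There were 2,000 to 3,000 trials per setting. Assumed covariates: normal age and weight, sex 50%, smoking 25%, drinking 50%. The candidates were two-way terms only, selected either by forward AIC or by testing each term singly against the main-effects model and keeping all that lowered AIC. The selected model was then tested at nominal 0.05 as if prespecified.

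Results at N = 50:

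| Candidates and test | Singly | Forward |
| --- | --- | --- |
| No selection (main effects only) | 5.0% | 5.0% |
| All two-way, treatment coefficient, centred | 7.2% | 9.9% |
| All two-way, treatment coefficient, uncentred | 14.9% | 24.3% |
| All two-way, joint test of all treatment terms | 18.1% | 31.5% |
| All two-way, any treatment term significant (uncentred) | 24.7% | 41.3% |
| Covariate-by-covariate terms only, treatment coefficient | 6.8% | 8.0% |
| Treatment interactions only, treatment coefficient, centred | 5.7% | 5.8% |

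With all two-way terms as candidates, the mean number of interactions kept was 2.94 (singly) and 3.28 (forward). A treatment interaction was kept in 66% and 67% of trials. The single-test figures agree with the finite-sample calculation above (2.96 and 0.67).

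At N = 40 the main-effects model gave 4.2% to 4.3%. With all two-way candidates, the treatment coefficient gave 7.3% to 9.9% centred and 13.3% to 28.0% uncentred, and the joint test gave 15.4% to 33.9%. Monte Carlo standard error is about 0.4 to 0.5 points near 5% and about 1 point near 30%.

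**Sensitivity to the assumptions.** Runs with other assumed covariates (age mean 60, SD 12; weight mean 60, SD 10; smoking 20%; drinking 40%) gave 7% to 11% centred and 14% to 29% uncentred over N = 40 to 50, with 5% to 6% for no selection. A further set of centred runs gave 7.7% to 8.9% at N = 50 and 8.1% to 12.1% at N = 40. In that set at least one interaction was kept in 95% to 97% of trials.

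**The case against.** The strongest reply is that the rule is written down in advance, that the trial is a pilot, and that the large error rates come from choices the protocol does not prescribe. Nobody is told to read an uncentred coefficient at age 0, or to treat any significant treatment term as an effect. A statistical analysis plan could specify centring and a contrast averaged over the covariates, and in an identity-link model that contrast still targets the average difference between arms. On the mildest reading (treatment interactions only, centred, main coefficient) the error is 5.7% to 5.8%, close to nominal. The 5% level itself is not in the protocol, and the covariate distributions are assumed.

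Much of this stands as a limit on the size. The 5% level is a convention adopted here. The figures of 13% and above apply only under particular coding or a particular choice of test, and a model found by a stated algorithm is not strictly unplanned.

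It does not remove the defect. Prespecifying a search does not correct the error rate of the test that follows it. The near-nominal reading requires narrowing the rule to treatment terms, which its wording does not do. With all two-way terms and centred covariates the excess remains, and it remains at 6.8% to 8.0% even if only covariate-by-covariate terms are searched. An analysis plan that followed the protocol would inherit the rule. The pilot label does not help either, because the stated primary objective is an efficacy comparison.

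**Conclusion.** The concern holds and should be corrected before the primary analysis is run. This is a stated rule, not a missing detail, and nothing elsewhere in the protocol limits or overrides it.

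With every two-way interaction as a candidate and centred covariates, the type I error of the treatment test is about 7% to 12% instead of an assumed 5%. It is about 13% to 29% if covariates are uncentred, and higher still if any significant treatment term is read as an effect. Without selection the same model gives about 5%, so the selection step causes the excess.

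The exact size depends on the assumed covariate distributions, the number analysed (40 to 50) and the choices the text leaves open. Only two-way terms were simulated; admitting higher-order terms would widen the search. The rates apply to each outcome separately. Apart from the error rate, a treatment interaction would enter by chance in about two thirds of null trials, and the protocol does not say which treatment contrast would then be reported.

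**What to change.** Delete the AIC sentence from Statistical tests. State that the primary model contains treatment and the listed covariates as main effects only, with no data-driven terms. State that the treatment difference with its 95% CI from that model is the primary result for each primary outcome, and give the significance level and sidedness.

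If effect modification is of interest, name one or two treatment-by-covariate terms in advance and report them separately as exploratory. Adding the baseline score as a covariate is worth considering for precision, but this repair does not depend on it.

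The cost is a few lines of text in one section, with no change to data collection or sample size. The trial gives up the ability to claim subgroup effects found by search from the primary model.
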